### 2.7. Outcome Measures and Data Collection

Primary outcomes focus on adherence and user experience, measured by app usage frequency/duration and wearable device data. User experience is evaluated using validated tools such as the User Experience Questionnaire [20,21].

Secondary outcomes include anthropometric measures, biological markers, physical activity, and dietary patterns, assessed through wearables and validated questionnaires, as described below and summarized in Table 4.

Anthropometric measurements: Body weight, height, waist circumference, hip and thigh circumferences will be taken, and body composition will be conducted following standardized procedures, with specific equipment varying by country. Body weight will be recorded with participants wearing light clothing and no shoes. A predetermined weight will be subtracted to account for clothing. Height will be measured to the nearest millimeter with participants standing upright and maintaining the Frankfurt Horizontal Plane. Body mass index (BMI) will be calculated as weight (kg) divided by the square of height (m^2^). Waist circumference (WC) and hip circumference (HC) will be measured in duplicate using an anthropometric tape, ensuring proper positioning and participant posture. WC will be assessed at the midpoint between the lowest rib and the iliac crest, while HC will be measured at the widest part of the hips, with the tape placed horizontally around the body. Participants will stand upright with feet together, and the average of the two measurements will be recorded for analysis [22].

Biological samples: The participants may provide saliva, urine, and blood samples. Urine samples will be collected the day after completing a 24 h Recall (24hR) to accurately assess dietary biomarkers. Additional assessments, including markers of oxidative stress and inflammation (Table 4), will be performed using commercial ELISA kits according to the manufacturer’s instructions [23,24,25].

Questionnaires: Validated questionnaires will be via REDCap [26], and include the following:24hR (24-Hour Recall): Completed three times to assess dietary intake [27].BFI-10 (Big Five Inventory—10 Items): A personality assessment tool [28].IPAQ-S (International Physical Activity Questionnaire—Short Form): Measures physical activity levels [29].PHQ-9 (Patient Health Questionnaire—9): Evaluates symptoms of depression [30].PSQI (Pittsburgh Sleep Quality Index): Assesses sleep quality and disturbances [31].UEQ (User Experience Questionnaire): Measures user experience with digital platforms or interventions [32,33].WHOQOL (World Health Organization Quality of Life): Assesses quality of life across different domains [34].FFQ (Food Frequency Questionnaire) of 143 items: Evaluates dietary intake over a specified period [35,36,37,38].

All questionnaire data within REDCap will be securely stored on the Luxembourg Institute of Health (LIH) Cloud, with access controlled by LIH’s IT Department. Wearable device data (from Samsung or Garmin smartwatches) and GameBus information will be stored on the GameBus server, managed by the University of Eindhoven, Netherlands. Nutrida data will be stored on a secure EU-based server provided by NIUM (Amazon). Data from the HDT and calendar application will be housed on a server managed by the Luxembourg Institute of Science and Technology (LIST). Garmin smartwatches will store data directly on the device and smartphone, while Samsung data will not be stored on external company servers outside Europe or on University of Eindhoven servers. Calendar event data is securely stored on servers at LIST, Luxembourg.

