### 2.2. Population: Inclusion and Exclusion Criteria

The pilot trial usually involves 30 young adults of both sexes per country; however, the final number of participants depends on each country, and there are a total of approximately 351 participants (Table 1). Inclusion criteria are age of 18–25 years, residence in the regions where the trials are conducted, BMI between 18.5 and 29.9 kg/m^2^ (normal weight to overweight), willingness to participate, ownership of a smartphone, and basic mobile application skills.

Exclusion criteria include individuals with obesity (BMI > 30.0 kg/m^2^), chronic conditions such as cancer, Parkinson’s disease, or other illnesses requiring specific treatments or significantly affecting normal physiology (e.g., metabolic disorders), cognitive impairments (e.g., Alzheimer’s disease), inability to live independently, adherence to specific diets, or inability to provide voluntary informed consent. However, individuals being treated for conditions such as type 2 diabetes, hypertension, or elevated blood lipids (e.g., triglycerides, cholesterol) will be included to ensure the recruitment reflects the typical demographic. If the drop-out or discontinuation rate exceeds 10%, additional participants will be recruited to maintain a minimum sample size of 20 participants per study site.

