The Gamebus Application	Promotes healthy lifestyle behavior, such as physical activity (e.g., walking and step counting), diet (e.g., preparing healthy meals, increasing the consumption of fruits and vegetables), or social participation (e.g., participating in cultural activities). The app uses gamification techniques (e.g., earning points, unlocking levels, competing on leaderboards) to motivate engagement. Developed by the Technical University of Eindhoven, GameBus serves as a prototype health data management platform, enhancing user engagement through mobile health (mHealth) platforms [19]. It includes an REST API based on Java Spring, an open-source web app frontend (using Ionic), and a restricted interface for smartwatches. Additional information can be found at the following website: https://blog.gamebus.eu/.
The Nutrida Application and Recipes	Provides personalized weekly meal plans, tailored to preferences, budget, allergies, and caloric requirements. The meal recommendation system is based on the Active Assisted Living (AAL) project, LIFANA, and has been further developed by the Nutrida app, created by NIUM, a University of Luxembourg spin-off (Esch-sur Alzette, Luxembourg), in collaboration with the Luxembourg Institute of Science and Technology (LIST) and the European Federation of the Association of Dieticians (EFAD), which integrates regional recipes into the app. Obtained data will be stored in secure Amazon servers in Europe, subcontracted by NIUM.
Wearable Device	Participants use either the Samsung Galaxy Active 2 smartwatch or the Garmin Vivosmart 5 fitness tracker to monitor 24 h movement, step count, sleep, pulse, and heart rate. The Samsung Galaxy Activity 2 smartwatches do not collect sleep data; also, heart rate and pulse are not measured continuously, and it can collect emotional states via the experience sampling method (as well as GPS tracking). Both devices comply with General Data Protection Regulation (GDPR), ensuring data privacy. The final choice of device will depend on the study’s specific requirements, as both collect similar data.
Samsung Galaxy Watch Active 2 Experiencer or Garmin Vivosmart 5 App	Data collected through Samsung/Garmin App will be stored, ensuring compliance with GDPR and utilize FHIR (Fast Healthcare Interoperability Resources) for FAIR (Findable, Accessible, Interoperable, and Reusable) data management.

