Actigraph Accelerometers	Participants will be required to wear an ActiGraph accelerometer (ActiGraph wGT3X-B; ActiGraph LLC, Pensacola, FL, USA) continuously for nine consecutive days to objectively assess their physical activity levels and sedentary behavior. This device will provide detailed data on movement patterns, energy expenditure, and sleep–wake cycles, allowing for a comprehensive analysis of participants’ activity and rest periods. To ensure data accuracy, participants will be instructed on proper device placement and usage.
Calendar Web Application	Developed by EU HealthyW8 partner VirTech (Bulgaria), this application enables the study leader to schedule local events and inform participants. The event data is securely stored on servers at LIST, Luxembourg.
REDCap (Research Electronic Data Capture), VanDerBilt University (USA)	Used for completing intervention questionnaires. Additional information can be found at the following website: https://project-redcap.org/. The event data is securely stored on servers at LIST, Luxembourg.

**Table 3 jpm-15-00625-t003:** Tools used by each participating country in the young adults’ pilot study.

Country, Partner	Bulgaria, RCNE	Germany, BIPS/DFKI	Italy, USG	Netherlands, TU/e	Portugal, UC	Portugal, UEV	Spain, CITA	Spain, IDISBA
Length of intervention (months)	3	3	1.5	1–2	3	3	3	3
Length of run-in time	6	6	6	1	2	2	2	2
Gamebus	Yes	Yes	Yes	Yes	Yes	Yes	Yes	Yes
Nutrida	Yes	Yes	Yes	Yes	Yes	Yes	Yes	Yes
Wearable	Garmin	Samsung	Garmin	Samsung	Samsung	Garmin	Garmin	Garmin
Experiencer	No	No	No	Yes	Yes	No	No	No
Accelerometer	Yes	Yes	No	No	No	Yes	No	Yes
Calendar	Yes	Yes	Yes	No	No	Yes	Yes	Yes
Questionnaires	Yes	Yes	Yes	Yes	Yes	Yes	Yes	Yes
Biological samples and measures	Yes	No	No	No	No	Yes	No	Yes

Abbreviations: RCNE: Regional Cluster North-East; BIPS/DFKI: Leibniz-Institut fur Praventionsforschung und Epidemiologia-BIPS GmbH/Deutsches Forschungzentrum fur Kunstliche Intelligenz GmbH; USG: Universitá Degli Studi di Scienze Gastronomiche; TU/e: Eindhoven University of Technology; UC: Universidade de Coimbra; UEV: Universidade de Évora; CITA: Centro de Investigación y Tecnología Agroalimentaria de Aragón; IDISBA: Fundació Institut d’Investigació Sanitària de les Illes Balears.

**Table 4 jpm-15-00625-t004:** Measures included in pilot studies of each team.

Marker Class	Marker	Bulgaria, RCNE	Germany, BIPS/DFKI	Italy, USG	Netherlands, TU/e	Portugal, UC	Portugal, UEV	Spain, CITA	Spain, IDISBA

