Anthropometrics	Height, weight, BMI	Yes	No	Yes	Yes	Yes	Yes	Yes	Yes
	Waist and hip circumference and ratio	No	No	Yes	No	Yes	Yes	No	Yes
	%body fat	No	No	Yes	No	Yes	Yes	No	Yes
	Visceral fat	No	No	No	No	Yes	Yes	No	Yes
	Thigh circumference	No	No	Yes	No	Yes	Yes	No	Yes
Clinical	Heart frequency	No	No	No	No	Yes	Yes	No	Yes
	Blood pressure (systolic and diastolic)	No	No	No	No	Yes	Yes	No	Yes
PA	Accelerometer	Yes	No	No	No	Yes	Yes	No	Yes
	IPAQ	Yes	Yes	Yes	Yes	Yes	Yes	Yes	Yes
Fitness	Hand grip strength, step-up test	No	No	No	No	No	No	No	No
Dietary patterns	FFQ	Yes	Yes	Yes	No	Yes	Yes	Yes	Yes
	24 h recall	Yes	Yes	Yes	No *	Yes	Yes	Yes	Yes
	Mediterranean eating patterns (MEDAS-14) **	No	No	Yes	Yes	Yes	Yes	Yes	Yes
General questionnaires	Quality of life (WHOQOL-Bref 26 items) **	Yes	Yes	Yes	Yes	Yes	Yes	No	Yes
	UEQ+ (26 items)	Yes	Yes	No	Yes	Yes	Yes	Yes	Yes
	Depression (PHQ-9; nine items) **	Yes	Yes	Yes	No	Yes	Yes	No	Yes
	Sleeping patterns (e.g., Pittsburgh Sleep Quality Index) **	No	Yes	Yes	No	Yes	Yes	No	Yes
	Intrinsic motivation (IMI seven items), **	Yes	No	No	Yes	Yes	Yes	No	Yes
	Smoking (Fagerstrom six items) **	No	Yes	Yes	No	No	No	No	No
	Alcohol intake (Audit 10 items) **	No	Yes	Yes	No	No	No	No	No
	Personality traits (BFI-10 scale 10 items) **	Yes	No	Yes	Yes	Yes	Yes	Yes	Yes
Biomarkers, inflammation	Cytokines (adiponectin, TNF-α, IL6, IL1-β, CRP)	No	No	No	No	No	No	No	Yes
Biomarkers, oxidative stress	F2- isoprostanes, malondialdehyde, DNA/RNA breakdown products, antioxidant activity (FRAP, ABTS, MDA)	No	No	No	No	No	No	No	Yes
Biomarkers of nutrient intakes	Blood cell counts, albumin, prealbumin,	No	No	No	No	Yes	Yes	No	Yes
Glucose metabolism	HbA1c and fasting blood glucose, insulin, HOMA-IR	No	No	No	No	Yes	Yes	No	Yes
Lipid profile	Total cholesterol, HDL-C, LDL-C, triglycerides	No	No	No	No	Yes	Yes	No	Yes
Urinary markers	Uric acid, urinary creatinine, urinary sodium,	No	No	No	No	Yes	Yes	No	Yes
Saliva	Cortisol	No	No	No	No	Yes	Yes	No	Yes
HLRS	Nutrida-app: Personalized meal recommender plan (based on age, gender, PA, dietary restrictions, culinary/ cultural personal preferences and local dishes, budget…)	Yes	Yes	Yes	Yes	Yes	Yes	Yes	Yes
	GameBus: Application that promotes healthy lifestyle through games and tasks linked to Nutrida and smartwatches	Yes	Yes	Yes	Yes	Yes	Yes	Yes	Yes
	Smartwatch: To register step count, pulse, sleep quality	Yes	Yes	Yes	No	Yes	Yes	No	Yes
	Calendar function to schedule social events for the participants	Yes	Yes	Yes	No	No	No	Yes	No

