	UEQ+ (26 items)	Yes	Yes	No	Yes	Yes	Yes	Yes	Yes
Open Stakeholder Platform	Health video clips, recipes, lifestyle recommendations	No	No	Yes	Yes	Yes	Yes	No	Yes

* It was performed in a separate study. ** Self-applied questionnaires.

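### Table 4 omits the only named user-experience questionnaire at the largest site (Italy, 101 of 351), and Tables 3 and 4 disagree on who wears a smartwatch

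*Protocol article*

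**What the plan says.** Section 2.7 defines the primary outcomes: "Primary outcomes focus on adherence and user experience, measured by app usage frequency/duration and wearable device data". It continues: "User experience is evaluated using validated tools such as the User Experience Questionnaire". No other user-experience tool is named.

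The site columns of Tables 3 and 4 run in the same order: Bulgaria (RCNE), Germany (BIPS/DFKI), Italy (USG), Netherlands (TU/e), Portugal (UC, Coimbra), Portugal (UEV), Spain (CITA), Spain (IDISBA).

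- Table 4, user experience: "UEQ+ (26 items) Yes Yes No Yes Yes Yes Yes Yes". The row appears twice, under general questionnaires and under HLRS, with the same cells. The third cell is Italy.
- Table 4, smartwatch: "Smartwatch: To register step count, pulse, sleep quality Yes Yes Yes No Yes Yes No Yes". The two No cells are TU/e and CITA.
- Table 3, wearable: "Wearable Garmin Samsung Garmin Samsung Samsung Garmin Garmin Garmin". Every site has a device; TU/e has a Samsung and CITA a Garmin.
- Table 2, wearable device: "The Samsung Galaxy Activity 2 smartwatches do not collect sleep data".
- Table 4, anthropometrics: "Height, weight, BMI Yes No Yes". The No is Germany, the only site so marked in that row.

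Section 2.2 makes a BMI of 18.5 to 29.9 kg/m² an inclusion criterion. Section 2.6 bases eligibility on anthropometric measurements together with screening questionnaires. On size, Section 2.2 states that "there are a total of approximately 351 participants (Table 1").

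**The concern.** This is a feasibility pilot meant to prepare a 12-month controlled study, so user experience is one of its main products. If the only named instrument is not given in Italy, the user-experience result says nothing about the largest site. Section 3 rules out imputation, so the gap cannot be closed at analysis.

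The smartwatch problem is of a different kind. Two tables state opposite things about the same two sites, and a reader cannot tell whether those participants contribute wearable data to the adherence outcome.

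The remaining items matter less. They are an eligibility criterion with no recorded measurement behind it at one site, and further rows where the two tables, or Tables 2 and 4, cannot both be right.

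**Working it through.** **Reproducing the total.** The Table 1 enrolment targets, in the column order above, are 30 + 30 + 101 + 40 + 30 + 30 + 60 + 30 = 351, which matches Section 2.2. The required completers are 20 + 15 + 52 + 20 + 15 + 15 + 25 + 20 = 182.

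**Share affected, by item** (enrolment target at the sites concerned ÷ 351; completers ÷ 182):

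| Item | Sites | Enrolment | Required completers |
|---|---|---|---|
| User-experience questionnaire marked No | Italy | 101/351 = 28.8% | 52/182 = 28.6% |
| Smartwatch contradictory | TU/e, CITA | 40 + 60 = 100; 100/351 = 28.5% | 20 + 25 = 45; 45/182 = 24.7% |
| Height, weight, BMI marked No | Germany | 30/351 = 8.5% | 15/182 = 8.2% |

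**Resulting denominators.**

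- User experience, as Table 4 stands: 351 − 101 = 250 enrolled, 182 − 52 = 130 completers.
- Wearable data: 351 enrolled if Table 3 is right; 351 − 100 = 251 if Table 4 is right. For completers, 182 or 182 − 45 = 137.
- App usage: GameBus and Nutrida are Yes at all eight sites in both tables, so 351 stands.

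**Other cells set side by side.**

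| Item | Site | Table 3 | Table 4 |
|---|---|---|---|
| Accelerometer | Germany | Yes | No |
| Accelerometer | Coimbra | No | Yes |
| Biological samples | Bulgaria | Yes | No in every biomarker row |
| Biological samples | Coimbra | No | Yes for nutrient, glucose, lipid, urine and saliva markers |
| Smartwatch sleep | Germany, Coimbra | Samsung | Yes, although Table 2 says this watch collects no sleep |

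For biological samples the planned total does not change. Table 3 gives Bulgaria, UEV and IDISBA, 30 + 30 + 30 = 90; Table 4 gives Coimbra, UEV and IDISBA, also 90. What is unsettled is which sites, not how many people.

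**Footnotes.** Table 4 has two: one says that the Dutch 24 h recall was done in a separate study, the other marks self-applied questionnaires. Neither explains any cell above.

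**The case against.** The best defence is that the core of the primary outcome is intact and the variation is open. The sample size in Section 3 rests on HLRS use, which every site collects. The Italian gap is shown twice in Table 4, Sections 2.1 and 2.5 announce local adaptations, and the wording in Section 2.7 leaves room for other user-experience tools. The abstract defines the primary outcomes through app usage and participant feedback without mentioning wearables, and Section 2.7 also uses wearables for secondary outcomes.

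Most of this stands. It limits the point to the questionnaire and the wearable part of adherence, and power is not in question. It does not remove the point. No alternative user-experience tool is listed for Italy, and local adaptation can explain why sites differ but not why two tables disagree about the same site.

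Several stronger readings are tempting but not supported:

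- *That a primary instrument is absent for 57% of participants.* The figure is (101 + 100)/351 = 57.3%. It adds a marked omission in Italy to an unresolved contradiction at TU/e and CITA. No site is affected on both instruments, and on the abstract's definition only the first counts.
- *That seven sites will be presented as eight.* Nowhere does the article present questionnaire results over eight sites or 351 people.
- *That eligibility cannot be checked in Germany.* Section 2.4 describes an online screening questionnaire, which could collect self-reported height and weight, and Table 4 need not describe screening. The tension is with Section 2.6, which relies on measurements.
- *That pooled sleep or heart-rate results will mix unlike devices.* No such pooled analysis is stated, and Section 2.7 assigns sleep to a questionnaire (PSQI). How to analyse wearable data by device may be settled in an analysis plan that is not shown.

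**Conclusion.** The point holds in a limited form. A named primary instrument is marked as not collected at the largest site (28.8% of planned enrolment), with no stated substitute. The wearable part of adherence, as Section 2.7 defines it, has no settled denominator because the tables contradict each other for 28.5%. The German BMI entry (30 participants) conflicts with the eligibility assessment unless self-report is intended. The accelerometer, biological-sample and smartwatch-sleep rows need correction but carry less weight.

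This rests on three assumptions: that the Yes/No cells are as the authors intended, that Table 1 targets are the right weights, and that Section 2.7 rather than the abstract governs whether wearables are primary. If the abstract governs, the smartwatch conflict is still an inconsistency, but not one in a primary outcome.

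**What to change.** - **Italy:** administer the user-experience questionnaire at its final visit through REDCap, which is already the route for questionnaires. Table 3 gives Italy a 1.5-month intervention against 3 months at most sites, so report the Italian scores with that shorter exposure noted. Use one name for the instrument: the text says UEQ and Table 4 says UEQ+.
- **Tables 3 and 4:** reconcile the smartwatch rows (TU/e, CITA), the accelerometer rows (Germany, Coimbra) and the biological-sample rows (Bulgaria, Coimbra). Remove smartwatch sleep from the Samsung sites.
- **Germany:** record height and weight at screening, or state that BMI eligibility there is self-reported.
- **Primary outcomes:** make the abstract and Section 2.7 agree on whether wearable data are primary, and state the actual denominator beside each primary instrument, so that 351 is not read as applying to all of them.

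The cost is one self-completed 26-item form in Italy, one height and weight entry in Germany, and table corrections, with possibly a minor ethics notification at those two sites. If collection in Italy cannot change, stating the reduced denominator (250 enrolled, 130 completers) and the reason costs almost nothing.

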## 3. Statistics

Sample Size Calculation: The study hypothesizes that the use of HLRS (≥45 min per week) will not decrease by more than 20% over the 3-month intervention period. Assuming a 30% standard deviation in usage, a 0.05 significance level, and 80% power, 20 participants would be required for a paired design. To compensate for an expected 33% attrition, 30 participants will be recruited, ensuring sufficient power. An equal distribution of males and females will be targeted to enhance the generalizability of the findings.

Handling of Missing Data and Dropout: No imputation will be performed for missing data. Participants who withdraw will be excluded from further analysis beyond their last available data. In order to maintain sample size and statistical power, replacements will be made as necessary, ensuring at least 20 participants complete the study. This method safeguards the integrity of the data and minimizes potential bias.

Data Analysis: Normality of the data will be assessed through Q-Q plots and Kolmogorov–Smirnov tests. Non-normally distributed data will be analyzed using non-parametric methods such as the Friedman test, followed by pairwise comparisons, and log transformations if appropriate. A significant level of *p* < 0.05 will be considered. Data will be analyzed using SPSS (version 25.0) and R (version 4.4.1). Since outcomes will be mainly descriptive, simple and descriptive statistics will summarize baseline participant characteristics, and changes over time will be assessed using paired t-tests, to evaluate the impact of the intervention on health outcomes.

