### 2.6. Follow-Up and Data Collection

The study spans 90 days (3 months) and is structured into five phases: enrollment (Dx), baseline visit (Day 0), and final visit (Day 90) in most of the participating partners. Data collection occurs at baseline and final visits, with regular check-ins via phone calls, or in-person meetings to maintain engagement. Figure 1 summarizes the timeline and interventions at each stage. Each study phase (outlined in Table 4) is described as follows:Enrollment visit (Dx): Informed consent (after receiving written and verbal information about the study’s objectives, risks, and benefits), eligibility assessment (assessed based on anthropometric measurements, and screening questionnaires on general health and lifestyle), and meeting inclusion criteria.Baseline visit (Day 0): Anthropometric data, baseline questionnaires, biological samples (blood, urine, and saliva, where applicable), and instructions on using the HLRS platform. Recommendations will be adapted to the previously diagnosed health status, A1c levels or blood pressure of the participant. Participants will receive instructions on using the HLRS platform.Final visit (Day 90): Repeat assessments and questionnaires to evaluate changes over the study.

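### The usage hypothesis is a 20% limit on decline, but every change test named in the article tests for zero change and none is set against 20%

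*Protocol article*

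**What the plan says.** Section 3 of the protocol article (Sample Size Calculation) states the study's one quantified hypothesis: "the use of HLRS (≥45 min per week) will not decrease by more than 20% over the 3-month intervention period". The sample size follows from it: "Assuming a 30% standard deviation in usage, a 0.05 significance level, and 80% power, 20 participants would be required for a paired design". The allowance for loss is then added: "To compensate for an expected 33% attrition, 30 participants will be recruited, ensuring sufficient power".

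Under Data Analysis in the same section, "changes over time will be assessed using paired t-tests, to evaluate the impact of the intervention on health outcomes". For non-normal data the article names the Friedman test with pairwise comparisons. Significance is set at p<0.05. No reference value of 20%, confidence-limit rule or success criterion for usage appears. The section also describes the outcomes as mainly descriptive.

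Section 2.7 makes adherence, measured by app usage and wearable data, a primary outcome. Section 2.6 places data collection at the baseline and final visits and says of the Day 0 visit that "Participants will receive instructions on using the HLRS platform".

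**The concern.** A hypothesis that use will not fall by more than a set amount has the form of a non-inferiority claim. Its null is a fall of 20% or more, and the data support it only by excluding that fall. A paired t-test or Friedman test in standard form asks whether there was any change at all. The two questions can give opposite answers. In a small sample, failing to detect a change does not show that the change is under 20%. In a large sample, a fall well inside the limit can be statistically significant.

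Usage is a primary outcome and the basis of the sample size, so this touches the main claim that the pilot can make. Two related items are also loose. The article does not say which early period of use the final use is compared with. It also attaches a threshold of 45 minutes per week to a relative change without saying which of the two decides the result.

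**Working it through.** **Inputs.** From Section 3: limit 20%, SD 30%, alpha 0.05 (sidedness not stated), power 80%, n=20 evaluable and 30 recruited. From Table 1: required completers by site of 20, 15, 52, 20, 15, 15, 25 and 20, which sum to 182. From Table 3: the intervention lasts 1.5 months in Italy (52 completers) and 1–2 months in the Netherlands (20), so the 3-month sites contribute 182 − 52 − 20 = 110. Assumption: 30% is the SD of the within-person change, in percentage points.

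**1. Reproducing the plan's figure.** For a paired t-test with difference 20 and SD 30, the standardised difference is 20/30 = 0.667. At two-sided 0.05 the noncentral t gives n=20 with power 80.7%. Recruitment: 20/(1 − 0.33) = 29.9, so 30. Both figures reproduce.

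The same n=20 and 80.7% arise in two ways:
- a zero-change test when the true fall is 20 points;
- a test against the 20% limit at one-sided 0.025 when the true fall is 0.

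In both, the distance between the truth and the null value is 20 points. The sample size therefore does not show which test was meant.

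**2. What the zero-change test would say about usage.** The smallest significant fall equals the CI half-width, t(0.975, n−1) × 30/√n. The largest observed fall that still excludes 20% is 20 minus that half-width.

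| n | Smallest significant fall | Largest observed fall that excludes 20% |
|---|---|---|
| 15 | 2.145 × 7.746 = 16.6 | 3.4 |
| 20 | 2.093 × 6.708 = 14.0 | 6.0 |
| 110 (3-month sites) | 1.982 × 2.860 = 5.7 | 14.3 |
| 182 (all sites) | 1.973 × 2.224 = 4.4 | 15.6 |

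- At n=20, an observed fall just under 14.0 points is non-significant, yet its 95% CI reaches 14.0 + 14.0, about 28 points. If the true fall is exactly 20 points, 19% of such studies are non-significant; if it is 15 points, 44% are.
- At n=15, the completer target at three sites, the figures are 16.6 and about 33 points.
- At n=110, an observed fall of 10 points has a 95% CI of 4.3 to 15.7. It meets the hypothesis and is also significant against zero. At n=182 the CI is 5.6 to 14.4, with the same double result.

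**3. Power for the hypothesis as written.** Tested against the 20% limit at one-sided 0.025, the noncentrality is (20 − true fall)/30 × √n.

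| True fall (assumed) | Power at n=20 | n for 80% power |
|---|---|---|
| 0 | 81% | 20 |
| 5 points | 56% | 34 |
| 10 points | 29% | 73 |

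The article gives no assumed true fall, so this is a range.

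**4. The SD.** If 30% is instead the SD at one occasion, the SD of change is 30 × √(2(1 − ρ)), where ρ is the within-person correlation. No correlation is given.

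| ρ | SD of change | n for a 20-point difference |
|---|---|---|
| 0 | 42.4 | 38 |
| 0.2 | 37.9 | 31 |
| 0.5 | 30.0 | 20 |
| 0.75 | 21.2 | 11 |

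The stated n=20 fits either a 30% SD of change or a 30% per-occasion SD with a correlation of 0.5. A higher correlation would need fewer participants.

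**The case against.** The strongest reply is that the paired t-tests are tied to health outcomes. Strictly, no test is assigned to usage, and a condensed article may leave that to a fuller document. The study is also a single-arm pilot whose outcomes are called mainly descriptive. Part of this stands. The article contains no rule under which a significant fall counts as failure or a non-significant one as success, and it does not say that usage is pooled. A reader might infer that the primary conclusion will rest on the wrong null; the text does not go that far, so the misreadings above are conditional. What remains is that the section sets a hypothesis, an alpha and a power for usage and then names only change tests that cannot answer it.

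Three further inferences are not supported:

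- That 80% power at n=20 holds only for a test against the limit. It holds equally for a zero-change test with a true fall of 20%.
- That usage has no possible starting value because the platform is introduced at Day 0. App usage can be compared early versus late, and Table 3 lists a run-in for every site, though without unit or content. The defect is an undefined reference window.
- That a group staying flat below 45 minutes would satisfy the hypothesis. That depends on reading the threshold as separate from the quantity tested. The wording is ambiguous and does not settle it.

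The pooled figure of 182 also needs care, because it includes two sites whose interventions are too short to show a 3-month change. The figure of 110 suits the hypothesis better.

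**Conclusion.** The mismatch between a 20% limit hypothesis and zero-change tests is real and lies in the article's own text. The sample size arithmetic is not in error.

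The consequences arise if the named tests are applied to usage. At site level they cannot confirm the hypothesis through non-significance. In a pooled analysis they can flag falls of roughly 5 points that lie well within the limit. These sizes rest on a 30% SD of the within-person change and on Table 1's required completers.

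Given the pilot setting, the absence of a written success rule and a remedy that needs only wording, this is something that should be fixed rather than a fatal flaw.

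**What to change.** - State that the hypothesis is supported only if the lower limit of the two-sided 95% CI for the mean relative change in weekly HLRS minutes lies above -20%.
- Fix an early on-platform reference window and a final window for that change (for example, weeks 1–2 against the last two weeks). Say how participants with near-zero early use are handled, since a relative change is unstable there.
- State whether the rule applies per site or pooled. If pooled, say how the sites with interventions shorter than 3 months are treated.
- Report alongside it the proportion of all enrolled participants with at least 45 minutes per week in the final window, with a 95% CI.
- If this test is adopted, restate the power sentence: 80% at n=20 assumes zero true decline and a 30% SD of the within-person change. If 30% is the per-occasion SD, give the correlation assumed.

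The cost is wording in the Statistics section. No extra data are needed, but the stated power becomes less favourable once any real decline is allowed for. The change should be made before usage data are examined.
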